### Study type and ethical issues

2.1

This clinical trial is a prospective, single-center, single-arm trial for patients with localized UTUC, which is ongoing at Nara Medical University Hospital. This trial complied with the Declaration of Helsinki regarding investigation in humans. Its ethical clearance and the final study protocol (version 1.0 on June 21st, 2021), including the subject information, informed consent forms, and associated documents, were approved by the Certified Review Board of Nara Medical University (institution ID: CRB5200002). Informed consent and written consent forms of patients are mandatory before study participation. This clinical trial was prospectively registered with the Japan Registry of Clinical Trials on June 28th, 2021 (the reference number: jRCTs051210042). The URL of trial registry record is found in https://jrct.niph.go.jp/latest-detail/jRCTs051210042.

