### Follow-up schedule and data collection

2.6

Patient data will be collected before and after the surgery; 1, 3, 6, 9, 12, 15, 18, 21, 24, and 27 months after the initial ALA-PDD-ULA; and at the end of the trial (Fig. 3). To improve monitoring adherence, the clinician will take time to explain the need for post-operative surveillance examination, including second-look URS, and encourage the participants to undergo routine cystoscopy, urine cytology, and CT/CT-U/MRI. The assessment includes patient-reported outcomes, such as the SF-8™, EORTC QLQ-C30, FACT-BL, International Prostate Symptom Score (IPSS), and overactive bladder symptom score (OABSS). The postoperative observational evaluation such as PROs can be discontinued upon participant request. The data will be documented in specific Case Report Forms for complete blood count, serum chemistry, cystoscopy, urine cytology, CT/CT-U/MRI, genitourinary adverse events (AEs), and other possible AEs using the Common Toxicity Criteria for Adverse Events (CTCAE v 5.0). When recurrence is suspected in imaging examinations, ALA-PDD-ureteroscopy is considered and, if recurrent tumor is present, ALA-PDD-ULA is additionally performed. AEs strongly related to the intervention of ALA-PDD-ULA are listed as follows: “Intraoperative urinary injury,” “Urinary tract infection,” “Fever,” “Renal hemorrhage,” “Hematuria,” “Creatinine increased”, “Urinary frequency”, “Photosensitivity”, “Hepatobiliary disorders”, “Urinary tract pain”, “Urinary urgency”, and “Dysuria”. Any other potential AEs are recorded and grouped into ‘related AEs’ or ‘unrelated AEs.’ When serious AEs occur, investigators report to the Safety Monitoring Committee.

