### Statistical analysis

2.10

Descriptive statistics will be computed for all study variables. EZR 1.54 (Saitama Medical Center, Jichi Medical University, 2020) and PRISM software version 7.00 (GraphPad Software, Inc., San Diego, CA, USA) were used for statistical analyses and data plotting, respectively. A two-sided P value of less than 0.05 will be considered to be statistically significant.

The full analysis set population and the per protocol set population will be separately analyzed for both the primary endpoint (two-year PFS rate) and survival outcomes listed in the secondary endpoints (Fig. 1). The per-protocol set population will be analyzed for the other secondary endpoints. The PFS of study population will be estimated by Kaplan Meier method, and 95% confidence interval (CI) will be calculated using Greenwood's formula for variance. When the lower limit of 95%CI of two-year PFS rate is more than 58% (threshold survival rate), the ALA-PDD-ULA is considered superior to the conventional ULA without PDD assistance. When the lower limit of 95%CI of two-year PFS rate is 58% or less, the ALA-PDD-ULA is considered not superior to the conventional ULA without PDD assistance. In addition, a sensitivity analysis of the primary endpoint will be performed using the Fine-Gray subdistribution hazard regression. This model considers patients who die of other causes (competing events) before recurrence or progression.

The amount of change in other post-operative observations over time will be analyzed using the repeated measures analysis of variance, Wilcoxon signed-rank sum test, or Mann-Whitney *U* test as appropriate. Mixed-effects models for repeated measures will be applied to detect multiple change-points in longitudinal data. To evaluate the diagnostic accuracy of UroVysion test, the result is compared to the pathological diagnosis obtained by URS biopsy. The sensitivity, specificity, positive predictive value, negative predictive value, and diagnostic accuracy are determined according to standard methods [23]. The sensitivities of UroVysion test and the combination with the conventional cytology are compared to that of conventional cytology alone using McNemar's test.

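### Repeated-measures ANOVA would drop patients whom the plan allows to become incomplete, while the mixed model that would keep them is assigned to finding change-points, which it does not do

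*Protocol article*

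**What the plan says.** The trial has one arm: "This clinical trial is a prospective, single-center, single-arm trial for patients with localized UTUC" (section 2.1). For outcomes other than survival and diagnostic accuracy, section 2.10 says that the amount of change over time will be "analyzed using the repeated measures analysis of variance, Wilcoxon signed-rank sum test, or Mann-Whitney" U test, whichever suits. The next sentence brings in a further method and gives it a purpose: "Mixed-effects models for repeated measures will be applied to detect multiple change-points in longitudinal data". On the analysis set, the same section says: "The per-protocol set population will be analyzed for the other secondary endpoints".

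Section 2.6 collects data before and after surgery, then "1, 3, 6, 9, 12, 15, 18, 21, 24, and 27 months after the initial ALA-PDD-ULA", and again at the end of the trial. The Fig. 3 legend has patients complete the questionnaires at each visit. Section 2.6 also provides that "The postoperative observational evaluation such as PROs can be discontinued upon participant request". That sentence counts patient-reported outcomes among the postoperative observations, and section 2.10 names no other method for them.

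**The concern.** Three of the four named methods sit badly with the design.

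- **Repeated-measures ANOVA.** In its classical form it needs a full row of visits per patient, and the plan itself foresees patients stopping the questionnaires.
- **Mixed model.** It is the one listed method that uses partial follow-up from every patient across all visits. Its stated task, however, is locating change-points, which is a different model.
- **Mann-Whitney.** It compares independent samples, whereas change over time in one arm is a within-patient quantity.

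At stake are the patient-reported and other longitudinal results. An analysis of complete patients only could rest on a fraction of an already small trial, and a real change after treatment could be missed.

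**Working it through.** **Inputs.** Enrolment of 20 is from section 2.7, where 14/(1 − 0.30) = 20. The 10 timed visits are from section 2.6; with baseline that makes 11 occasions, or more if the immediate postoperative and end-of-trial collections count. The plan states no missing rate, no within-patient correlation and no size for the per-protocol set. So the missing rate (2% to 10% per visit) and the correlation ρ (0.3 to 0.7) are assumptions, and 20 is the largest possible base. The plan gives no figure of its own to reproduce for these analyses.

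**1. Patients left in a complete-case ANOVA.** Assume baseline is always present and each of the 10 later visits is missing independently with probability m. The complete share is (1 − m)^10.

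| m | Share complete | Of 20 |
|---|---|---|
| 2% | 0.98^10 = 0.817 | 16.3 |
| 5% | 0.95^10 = 0.599 | 12.0 |
| 10% | 0.90^10 = 0.349 | 7.0 |

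Independence matters. If the same patients missed every post-baseline visit, the share would be 1 − m: 19 of 20 at 5% and 18 of 20 at 10%. Patients who stop for good fall between these cases, so the table leans towards the larger loss.

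**2. What the mixed model estimates.** For patient i at visit j, the model is y_ij = μ_j + b_i + e_ij. Its parameters are 11 visit means and the variance terms. None of them is the time at which a trajectory changes. A change-point model adds unknown times τ_k, for example through terms δ_k·max(0, t − τ_k), and no such model is named. Even if change-points could fall only on the 9 interior occasions, there are 9×8/2 = 36 placements for two and 9×8×7/6 = 84 for three. Twenty patients cannot support an unrestricted search of that kind.

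**3. Mann-Whitney, if used to compare visits.** For a difference in means, the unpaired variance is 2σ²/n and the paired variance is 2σ²(1 − ρ)/n. The unpaired standard error is therefore too large by a factor of 1/√(1 − ρ), which is 1.41 at ρ = 0.5. This is only a guide for a rank test, so the tests were also simulated: paired normal data, n = 20, 3,000 runs, nominal level 0.05, and a true change of 0 or 0.5 SD.

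| ρ | Type I error, Mann-Whitney | Type I error, signed-rank | Power at 0.5 SD, Mann-Whitney | Power at 0.5 SD, signed-rank |
|---|---|---|---|---|
| 0.3 | 0.022 | 0.048 | 0.29 | 0.43 |
| 0.5 | 0.008 | 0.045 | 0.29 | 0.54 |
| 0.7 | 0.001 | 0.047 | 0.24 | 0.76 |

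The error runs in the conservative direction: too few rejections, not too many.

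**The case against.** The best defence is that the plan already contains what it needs. The mixed model uses incomplete patients, the signed-rank test is properly paired, and the choice among the tests is left to what suits each variable. The change-point phrase may be a loose way of saying change at several time points. These are secondary outcomes in a 20-patient pilot whose only decision rule concerns two-year progression-free survival, and the missing rates above are assumed.

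Much of this stands, and it limits the point. It does not remove the ANOVA mismatch, and the mixed model's stated purpose is still wrong on either reading.

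Several stronger readings are tempting but unsupported:

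- A reader might infer that Mann-Whitney will be run between visits. The text does not say so. Comparing amounts of change between two sets of patients would be valid, although no such sets are defined.
- A reader might infer that the test will be picked after the data are seen. The article does not say when or how the choice is made.
- A reader might infer that complete patients would be the healthier ones. Section 2.6 gives no direction for the dropout.
- A reader might multiply five instruments by 10 visits and expect a run of false positives. No such set of baseline comparisons is planned.
- A reader might take 14 as the per-protocol size, or object to an unstructured covariance. Fourteen is the survival sample-size requirement, and no covariance structure is named.

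**Conclusion.** The point holds as a mismatch between named methods and the design, confined to the longitudinal secondary outcomes. Two parts follow from the text alone: classical repeated-measures ANOVA discards patients whom the plan allows to become incomplete, and a repeated-measures mixed model does not detect change-points. The Mann-Whitney part is conditional: the test is unsuitable for within-patient change, but misuse is not shown.

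The size cannot be fixed from the document. Under independent missingness of 5% (10%) per visit, about 60% (35%) of patients would be complete, and more than that if dropout clusters. The power loss for Mann-Whitney rests on assumed correlations and normal data. The primary analysis is unaffected.

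**What to change.** In section 2.10:

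1. Make one mixed model per scale the main analysis of change over time, with visit as a categorical factor and either a patient random effect or a simple structured covariance, fitted to all available visits. A simple structure is advised because an unstructured one over 11 occasions has 11×12/2 = 66 covariance parameters.
2. Report mean change from baseline with a 95% confidence interval at a few visits fixed in advance, for example 1, 12 and 24 months.
3. Keep the signed-rank test as a paired check.
4. Delete repeated-measures ANOVA and the change-point aim.
5. Limit Mann-Whitney to between-patient comparisons that are named in advance, or delete it.

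The cost is analysis wording only. The mixed model is already in the plan, and no visit, instrument or patient is added. The trial status section expects data collection to end in June 2026, so the change should be made before the analysis.

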**Methods:**

The FLUAM trial is a prospective, single-center, single-arm pilot trial to investigate the efficacy of 5-aminolevulinic acid-mediated photodynamic diagnosis (ALA-PDD)-assisted ULA for localized UTUC and the usefulness of the UroVysion® assay (multiprobe fluorescence in situ hybridization) as a monitoring test after the kidney-sparing treatment. After the screening and registration, a total of 20 patients with localized UTUC will undergo the initial ALA-PDD-assisted ULA followed by the second look ALA-PDD-assisted ureteroscopic examination. The primary endpoint is progression-free survival. Secondary endpoints include patient reported outcomes, diagnostic accuracy of UroVysion assay to detect tumor recurrence, adverse events, and safety of the intervention.

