**Fig. 3 fig3:**
[figure not shown]
Intervention and assessment schedule of the FLUAM trial. Follow-up visits and data collection should occur approximately 1, 3, 6, 9, 12, 15, 18, 21, 24, and 27 months from the initial surgery. Patients will complete a set of questionnaires at every visit, and follow-up information may be collected via medical charts. The Case Report Form will include information regarding past history, concomitant medications, and any medications taken after the treatment. Chest–abdomen–pelvis computed tomography (CT) and/or magnetic resonance imaging (MRI) should be performed for TNM classification. X, mandatory; (X), optional, ALA-PDD-ULA after 6 months is performed when the radiographic examination suspect tumor recurrence in the upper urinary tract. *hemoglobin, hematocrit, white blood cell count and fractions, platelet count; **aspartate transaminase (AST), alanine transaminase (ALT), γ-glutamyl transpeptidase (γ-GTP), total bilirubin, alkaline phosphatase (ALP), lactate dehydrogenase (LDH), total protein, albumin, serum creatinine, blood urea nitrogen, uric acid, total cholesterol, triglyceride, C-reactive protein (CRP), sodium, potassium, chloride; ***Urine dipstick test (specific gravity, pH, protein, glucose, bilirubin, urobilinogen, ketone body, and occult blood) and urine sediment test; †according to the Common Toxicity Criteria for Adverse Events (CTCAE v 5.0) translated into Japanese; †† questionnaires SF-8™, EORTC QLQ-C30, and FACT-BL. Abbreviations: BW, body weight; BT, body temperature; BP, blood pressure; ALA, 5-aminolevulinic acid; PDD, photodynamic diagnosis; ULA, ureteroscopy laser ablation; QOL, quality of life; IPSS, International Prostate Symptom Score; OABSS, overactive bladder symptom score.

To protect the patient's personal information, unique identification codes (FLUAM IDs) will be assigned to all patients. All the data will be protected in password-accessible electronic data files on secure servers before, during, and after the trial, and only investigators will be able to access the files. All data and documents will be deleted and discarded five years after the trial ends, unless the data are being used for another study.

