### Protocol of Fluorescence In Situ Hybridization (FISH) assay

2.9

As exploratory research, we evaluate the diagnostic accuracy of UroVysion test of voiding urine specimens during follow-up and upper urinary tract irrigation or catheterized urine obtained by URS. Sample preparation is performed according to the protocol for UroVysion® FISH bladder cancer assay (SRL, Inc., Tokyo, Japan). We transfer urine sediments into ThinPrep® PresevCyt® Solution containing 55% methanol (UV7) and subject fixed samples to the SRL laboratory. Trained observers who are blinded for clinicopathologic data assess enumeration of FISH signals. This assay enables the visualization of molecular alterations, including aneuploidy of chromosomes 3 (red), 7 (green), and 17 (aqua) and loss of locus 9p21 (gold), which are frequently seen in human bladder cancer. Specimens are considered to be positive for UroVysion test if four cells or more have a gain of 2 or more chromosomes (3, 7, or 17) or 12 cells or more have a loss of both copies of locus 9p21 among observed 25 morphologically abnormal cells [18,22].

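### After the second look, UroVysion is verified mainly where imaging is suspicious, so PPV and NPV from biopsied visits will not describe surveillance; the sensitivity-only test of the combination has a direction fixed by its rule

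*Protocol article*

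**What the plan says.** Section 2.9 describes the specimens: "we evaluate the diagnostic accuracy of UroVysion test of voiding urine specimens during follow-up and upper urinary tract irrigation or catheterized urine obtained by URS". Section 2.10 names the reference: "To evaluate the diagnostic accuracy of UroVysion test, the result is compared to the pathological diagnosis obtained by URS biopsy". It then derives sensitivity, specificity, PPV, NPV and overall accuracy by standard methods. It gives no reference status for a urine sample without a biopsy, and it does not separate the second look from later visits.

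Ureteroscopy comes about in two ways. The Abstract (Methods) plans the initial procedure for all 20 patients, "followed by the second look ALA-PDD-assisted ureteroscopic examination". For later follow-up, section 2.6 says: "When recurrence is suspected in imaging examinations, ALA-PDD-ureteroscopy is considered and, if recurrent tumor is present, ALA-PDD-ULA is additionally performed". The Fig. 3 legend adds, for the ablation procedure, "ALA-PDD-ULA after 6 months is performed when the radiographic examination suspect tumor recurrence in the upper urinary tract". Section 2.6 schedules ten visits, at months 1 to 27.

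On cytology, section 2.10 says: "The sensitivities of UroVysion test and the combination with the conventional cytology are compared to that of conventional cytology alone using McNemar's test".

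**The concern.** The Abstract gives the usefulness of UroVysion as a monitoring test as part of the trial's purpose and lists its accuracy as a secondary endpoint. The Introduction motivates this by the lack of a reliable non-invasive way to find recurrence after kidney-sparing treatment. The visits that matter most for that question are those where imaging is clear and the urine result would have to stand alone. Under the stated rule, after the second look, those are the visits least likely to have a reference result.

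Biopsied later visits are enriched for recurrence. PPV and NPV depend directly on the proportion with disease, so values taken from those visits describe a different population from patients under routine surveillance. PPV would look too good and NPV too poor.

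The second matter is the combination with cytology, whose feasibility as a detection marker is a stated aim in the Introduction. A test of sensitivity alone cannot show whether adding UroVysion is worthwhile, because the cost in specificity is left out.

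**Working it through.** The protocol gives no target or expected value for UroVysion accuracy, so there is no stated figure to reproduce. The check is a partial-verification calculation.

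**Inputs.** From the article: reference standard (2.10), trigger for later ureteroscopy (2.6), specimens (2.9). Assumed, because the article gives no values: UroVysion sensitivity/specificity 70%/85% or 50%/90%; probability of biopsy with/without recurrence 0.8/0.1 or 0.6/0.05; prevalence of recurrence at a tested visit 10%, 20% or 30.7%. The last is the lower end of the surgical-site recurrence range in the Introduction, used only as a high illustrative value per visit.

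**Formula.** Expected cell = P(disease status) × P(test result | disease status) × P(biopsy | disease status). PPV = TP/(TP+FP); NPV = TN/(TN+FN).

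**Prevalence 10%, 70%/85%.**

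- All visits verified: TP 0.070, FN 0.030, FP 0.135, TN 0.765. PPV = 0.070/0.205 = 34%; NPV = 0.765/0.795 = 96%.
- Biopsy 0.8/0.1: TP 0.056, FN 0.024, FP 0.0135, TN 0.0765. PPV = 0.056/0.0695 = 81%; NPV = 0.0765/0.1005 = 76%. Visits verified: 17%.
- Biopsy 0.6/0.05: TP 0.042, FN 0.018, FP 0.00675, TN 0.03825. PPV = 0.042/0.04875 = 86%; NPV = 0.03825/0.05625 = 68%. Visits verified: 10.5%.

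**All scenarios, PPV / NPV.**

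| Sens/spec | Prevalence | All verified | Biopsy 0.8/0.1 | Biopsy 0.6/0.05 |
|---|---|---|---|---|
| 70%/85% | 10% | 34% / 96% | 81% / 76% | 86% / 68% |
| 70%/85% | 20% | 54% / 92% | 90% / 59% | 93% / 49% |
| 70%/85% | 30.7% | 67% / 86% | 94% / 44% | 96% / 35% |
| 50%/90% | 10% | 36% / 94% | 82% / 67% | 87% / 57% |
| 50%/90% | 20% | 56% / 88% | 91% / 47% | 94% / 38% |
| 50%/90% | 30.7% | 69% / 80% | 95% / 34% | 96% / 25% |

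These figures describe imaging-triggered later visits, not a mixture with the second look.

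**Sensitivity and specificity.** In every row above they keep their assumed values, because the biopsy probability cancels within each disease group. They move only if biopsy also depends on the UroVysion result, or on a shared cause, given disease status. At 20% prevalence and 70%/85%:

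- P(biopsy | recurrence) 0.9 if UroVysion-positive and 0.5 if negative, as when both tests miss small tumours: sensitivity = 0.14×0.9/(0.14×0.9 + 0.06×0.5) = 0.126/0.156 = 81% instead of 70%.
- P(biopsy | no recurrence) 0.2 if UroVysion-positive and 0.1 if negative: specificity = 0.68×0.1/(0.68×0.1 + 0.12×0.2) = 0.068/0.092 = 74% instead of 85%.

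**Combination against cytology.** If either positive result counts, every cytology-positive case is also combination-positive, so the combination can never be less sensitive. If both must be positive, it can never be more sensitive. Under either rule all discordant pairs fall on one side. With b such pairs the exact two-sided p is 2 × 0.5^b: b = 5 gives 0.0625 and b = 6 gives 0.031.

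**The case against.** The strongest reply is that the selection is narrower than it looks. The second look is planned for everyone, and urine obtained at ureteroscopy is by definition paired with an examination. A reader might infer that the analysis describes UroVysion only in imaging-positive patients; the documents do not support that, and the claim holds only for later visits. Section 2.6 also says that ureteroscopy is considered on suspicious imaging, not that it is done only then. The Fig. 3 legend speaks of ablation rather than diagnostic ureteroscopy, and the figure itself is not shown, so the number of scheduled examinations cannot be confirmed. These points limit the reach of the concern but do not supply a reference for imaging-clear urine at later visits.

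A reader might also infer that specificity will be wrong. It need not be: no section names UroVysion as a trigger for ureteroscopy, and verification by imaging alone leaves both specificity and sensitivity unchanged if the two tests are independent given disease status.

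Three further inferences go too far:

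- That bladder-tumour cells in voided urine will be scored as false positives. This depends on how concurrent bladder tumours are handled, which an article may leave to the full protocol or SAP.
- That repeated specimens break McNemar's independence. This holds only if several specimens per patient are pooled, which is not stated.
- That the combination will look better whatever the data. Under an either-positive rule it can tie with cytology, and p below 0.05 needs six discordant pairs. The comparison of UroVysion alone with cytology is not constrained in direction.

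The missing combination rule is likewise no fault of an article. The point stands because the direction is fixed under either rule.

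Finally, section 2.9 calls this work exploratory, in a 20-patient pilot. That lowers the severity. It does not make the predictive values usable.

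**Conclusion.** The concern holds in this limited form. Section 2.10 fixes ureteroscopic biopsy as the only reference, while section 2.6 makes that reference depend largely on suspicious imaging after the second look. PPV and NPV pooled over biopsied visits would therefore not apply to surveillance. At 10% prevalence and 70%/85%, the shift is from 34% to 81–86% for PPV and from 96% to 76–68% for NPV. All accuracy and verification inputs are assumed; the direction is the same in every scenario tried, but the size is illustrative. Bias in sensitivity or specificity is possible but conditional. An overstated sensitivity would matter most, since that is what McNemar's test compares.

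The combination test cannot show whether adding UroVysion to cytology is worthwhile. Severity is modest, because this is a secondary endpoint described as exploratory and the primary PFS decision is untouched.

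**What to change.** - Make the second-look ureteroscopy the main accuracy analysis, with one specimen per patient and specimen type (voided; irrigation or catheterized). Use ureteroscopic findings plus biopsy as the reference, because a visually clear examination may yield no pathology.
- Report imaging-triggered later visits separately, with the number verified out of the number tested. Do not present their PPV and NPV as surveillance values.
- Use any composite reference built from the imaging, cystoscopy and ureteroscopy already collected only as a sensitivity analysis. It can label recurrences that imaging missed as disease-free and so turn true UroVysion positives into false positives.
- Replace the combination test by the paired difference in sensitivity together with the paired difference in specificity, each with a confidence interval.

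The change is to analysis wording and reporting; no procedure is added. The price is precision and scope. The main analysis has at most 20 patients and possibly few positives, so intervals will be wide, and the second look measures early residual disease more than late recurrence. The report should say so.

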The patients should be followed up closely in kidney-sparing management. Ureteroscopy with or without biopsy, cystoscopy, urinary cytology, and chest/abdominal/pelvic computed tomography (CT) or magnetic resonance imaging (MRI) are performed at regular intervals for surveillance [2,8]. Unfortunately, there is a significant lack of non-invasive reliable detection tools of urinary recurrent tumors in this treatment setting. Previous studies suggested that the UroVysion® test was a useful tool for the diagnosis not only of primary UTUC but recurrent UTUC after kidney-sparing surgery [17,18].

This prospective, single-center, single-arm pilot trial will investigate the efficacy and safety of ALA-PDD-assisted ULA for localized UTUC and the feasibility of UroVysion test combined with conventional urinary cytology as a detection marker of recurrent UTUC after the kidney-sparing surgery.

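### McNemar's test of UroVysion plus cytology against cytology alone can move in only one direction, and specificity is not formally compared

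*Protocol article*

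**What the plan says.** The protocol article, section 2.10, takes ureteroscopic biopsy as the reference standard: "the result is compared to the pathological diagnosis obtained by URS biopsy". It plans sensitivity, specificity, both predictive values and accuracy for UroVysion. It then fixes two formal comparisons: "The sensitivities of UroVysion test and the combination with the conventional cytology are compared to that of conventional cytology alone using" McNemar's test. So there are two contrasts, UroVysion against cytology and UroVysion combined with cytology against cytology. The threshold is general: "A two-sided P value of less than 0.05 will be considered to be statistically significant".

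The second contrast answers a named aim. The Introduction describes the feasibility of the "UroVysion test combined with conventional urinary cytology as a detection marker of recurrent UTUC after the kidney-sparing surgery". The article does not say whether the combination is positive when either test is positive or only when both are.

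Section 2.9 tests "voiding urine specimens during follow-up and upper urinary tract irrigation or catheterized urine obtained by URS" and labels the work exploratory; the Abstract lists UroVysion accuracy among the secondary endpoints. Section 2.6 schedules visits at "1, 3, 6, 9, 12, 15, 18, 21, 24, and 27 months after the initial ALA-PDD-ULA", and for later ureteroscopy says: "When recurrence is suspected in imaging examinations, ALA-PDD-ureteroscopy is considered". The article does not say whether the unit of analysis is the specimen or the patient.

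**The concern.** McNemar's test asks whether discordant pairs split evenly between two directions. That is meaningful only if both directions can occur. When one of the two tests is built from the other, one direction cannot occur.

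A significant result for the combination could then be reported as evidence that adding UroVysion improves detection of recurrence, although the sign of the difference was settled by the definition. Under an either-positive rule, any added test that is sometimes positive raises sensitivity, whether or not it carries information about tumour. The counterweight is what happens to specificity, and no formal comparison covers it.

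**Working it through.** The article gives no sample size, power or expected discordance for this comparison, so there is no figure of its own to reproduce.

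**Step 1: the discordant cells.** Only biopsy-positive pairs enter a sensitivity comparison. Let U be UroVysion and C be cytology.

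| U | C | Either-positive | Both-positive |
|---|---|---|---|
| + | + | + | + |
| + | − | + | − |
| − | + | + | − |
| − | − | − | − |

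- Either-positive: a negative combination with positive cytology never occurs. Discordance arises only from U+ C−, in favour of the combination.
- Both-positive: a positive combination with negative cytology never occurs. Discordance arises only from U− C+, against the combination.

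Under either rule, equal sensitivity would mean that no discordant pair can occur at all. A single one refutes that null logically, so the even-split reference distribution of McNemar's test does not describe it.

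**Step 2: what the P value measures.** With all k discordant pairs on one side:

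- Exact two-sided: P = 2 × 0.5^k. For k = 5, 2 × 0.03125 = 0.0625. For k = 6, 2 × 0.015625 = 0.031.
- Continuity-corrected chi-square: (k − 1)²/k. For k = 5, 16/5 = 3.2, P = 0.074. For k = 6, 25/6 = 4.17, P = 0.041.
- Uncorrected chi-square: k²/k = k. For k = 4, P = 0.046.

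Six discordant pairs reach 0.05 with the exact or corrected test, and four without correction.

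**Step 3: an added test unrelated to disease (assumed inputs, either-positive).** Let cytology sensitivity be s and let the added test be positive at random with probability r. Each biopsy-positive pair is discordant with probability (1 − s) × r. The exact test rejects when at least six of n pairs are discordant.

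| n | s | r | Expected discordant pairs | P(reject) |
|---|---|---|---|---|
| 20 | 0.3 | 0.5 | 20 × 0.7 × 0.5 = 7.0 | 0.76 |
| 20 | 0.5 | 0.3 | 20 × 0.5 × 0.3 = 3.0 | 0.07 |
| 10 | 0.3 | 0.5 | 10 × 0.7 × 0.5 = 3.5 | 0.095 |

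The article gives none of n, s or r, so the rate is illustrative and varies widely. The one-sided structure does not depend on them.

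**Step 4: specificity.** Among biopsy-negative pairs under either-positive, every cytology false positive is also a combination false positive. Specificity therefore stays equal if UroVysion adds no false positives, and otherwise falls. Under both-positive it can only stay equal or rise.

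**Step 5: repeat specimens (conditional).** For the other contrast, UroVysion alone against cytology alone, McNemar's test was simulated (10,000 runs) with 20 patients and equal assumed sensitivity of 0.5. Exact-test type I error by latent within-patient correlation:

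| Biopsy-positive pairs per patient | 0 | 0.3 | 0.5 | 0.8 |
|---|---|---|---|---|
| 1 | 0.019 | 0.022 | 0.022 | 0.022 |
| 2 | 0.028 | 0.050 | 0.057 | 0.083 |
| 4 | 0.037 | 0.092 | 0.14 | 0.21 |

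The number of pairs per patient and the correlation are assumptions; the article gives neither.

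**The case against.** Several points on the other side have force.

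- **The rule is not stated.** Under both-positive the sensitivity difference could only be zero or negative, and a false claim of improved sensitivity could not arise. This stands, so the risk of a spurious improvement is tied to the either-positive reading. It does not rescue the test, which is one-directional under both rules.
- **Specificity is in the plan.** It is to be estimated for UroVysion. That stands, but the sentence does not name the combination, and the only formal comparisons are of sensitivity. A reader might infer that a loss of specificity is certain; the supportable statement is that it cannot improve under either-positive.
- **Any comparison of sensitivity alone favours a test that is often positive.** True, and it applies to UroVysion alone against cytology as well. There, however, the result can go either way, and McNemar's test is suitable.
- **Repeat specimens.** A reader might infer, from the ten scheduled visits and several specimen types, that the plan treats repeat specimens from 20 patients as independent. The article does not say so. It does not fix the unit of analysis, which the full protocol or analysis plan may do. Voided urine at a visit without biopsy has no reference result, and only biopsy-positive pairs count towards sensitivity. Ten visits therefore do not yield ten pairs per patient, and a large variance inflation built on five to ten specimens each has no basis in the text.
- **The analysis is exploratory or secondary in a pilot trial.** This stands and limits the consequence.

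**Conclusion.** The point holds for the combination against cytology alone. The direction is fixed by construction under either natural rule, and the P value only counts discordant biopsy-positive pairs, with six enough for exact P = 0.031. Under either-positive, an uninformative added test could be declared an improvement. How often depends on unstated inputs: 7% to 76% across the two assumed settings with 20 pairs. These rest on independent pairs and random positivity of the added test.

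The point does not extend to UroVysion alone against cytology alone. The clustering concern is conditional: if several biopsy-positive pairs per patient are analysed as independent, type I error could exceed 0.05 (0.09 to 0.21 with four pairs and correlation 0.3 to 0.8); with one pair per patient it stays near 0.02. The change is worth making because this contrast addresses an aim stated in the Introduction. The primary endpoint and its sample size are not touched.

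**What to change.** 1. State when the combination counts as positive.
2. Drop McNemar's test for the combination against cytology alone. Report instead the paired difference in sensitivity (biopsy-positive pairs) together with the paired difference in specificity (biopsy-negative pairs), combination minus cytology alone, each with a 95% confidence interval.
3. Keep McNemar's test for UroVysion alone against cytology alone. It should not be confined to the second-look specimen, since that would shift the question from recurrence towards residual tumour.
4. If more than one biopsy-paired specimen per patient enters, use a method that respects clustering by patient, such as a clustered McNemar test or resampling of patients. With few biopsy-positive patients, resampling intervals may be unstable, and this should be acknowledged.

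The cost is analysis wording only; no new specimens or procedures are needed. There will be fewer nominally significant results, and the intervals will be wide: at most 20 patients contribute, and fewer have a positive biopsy if recurrence is not universal.
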